**EXPLORATORY OBJECTIVES:**

- Investigate the association of germ-line mutations that impact cancer predisposition.
- Investigate the role of germ-line mutations in predicting cancer outcome, toxicity and response to therapy.
- Evaluate pre-treatment, post-radiotherapy and, if applicable, metastatic or relapse tissue specimens for characteristics including DNA alterations, gene expression, protein expression, immunophenotype and intratumoral heterogeneity that may be predictive, prognostic or explain resistance.

**STUDY DESIGN:**

Single arm, non-randomized, phase II trial of preoperative hypofractionated radiation for extremity/trunk soft tissue sarcomas

**STRATIFICATION:**

Patients will be stratified into two cohorts according to the previous administration of neoadjuvant chemotherapy.

Cohort A: neoadjuvant radiotherapy alone

Cohort B: neoadjuvant chemotherapy and radiotherapy

**NUMBER OF PATIENTS**

**ORIGINAL COHORT: 51 patients**

**EXPANSION COHORT:**

**Cohort B: 41 patients (minimum)**

**Cohort A: 123 patients (minimum)**

---

*The study will be considered having achieved minimal accrual when both cohorts have reached their minimum enrollment. The total enrollment goal for the expansion cohort is 205 patients to account for an estimated 20% of patients having a screening failure or dropping out from the trial.*

#### **ELIGIBILITY CRITERIA:**

- Histologically confirmed soft tissue sarcoma of the extremity/trunk.
- Planning to undergo standard preoperative radiotherapy
- Resectable primary lesion (patients with pre-existing metastasis will be included if the primary lesion will be resected)
- Age  $\geq 12$
- KPS  $\geq 70$  or ECOG 0-2
- If a woman is of childbearing potential, a negative serum or urine pregnancy test must be documented.

#### **EXCLUSION CRITERIA:**

- Active treatment of a separate malignancy
- History of prior irradiation to the area to be treated

#### **INTERVENTION AND MODE OF DELIVERY:**

Hypofractionated radiation will be delivered in the pre-operative setting to patients with soft tissue sarcoma with external beam radiation therapy. Patients in cohort A will receive 6.0 Gy x 5 fractions delivered daily in 5 fractions. Patients in cohort B will receive 5.0 Gy x 5 fractions delivered daily in 5 fractions. Patients will not be treated on weekends or holidays as is standard practice for radiation treatments.

#### **DURATION OF INTERVENTION AND EVALUATION:**

Patients will be seen either by the radiation oncologist or the surgeon within the first 3 months after completion of pre-operative radiation therapy. For patients who live a distance far enough away from UCLA where travel would be challenging for the patient a phone follow-up will be considered acceptable. After this, follow-up will be performed every 6 months after the time of surgery for the 5 years after treatment. The patients will be followed both clinically and radiographically after treatment. Follow up phone or telemedicine visits will be allowed for some individuals where travel back to UCLA is challenging for the patient (i.e patients on this study may be enrolled who live in other states, such as Nevada). Surveillance imaging of the primary site by CT or MRI and of the chest by CT will be performed every 6 months for the first 2 years and then once at the end of year 3. Additional scans may be obtained at the investigators' discretion.

#### **STATISTICAL METHODS:**

### **1. Analysis of primary end point (major wound complication event).**

1.1 The comparison of major wound complication rates, defined as number of patients with major wound complication events over total number of patients, in cohorts A and B will be assessed using one- sided two-sample proportion test.

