In our initial cohort, we excluded patients receiving neoadjuvant chemotherapy, which is given in patients with highest-risk disease. Currently, patients receiving neoadjuvant chemotherapy receive conventional 5-week preoperative radiation therapy, or in some cases, an abbreviated 8-day course of 28 Gy(7). Now, we propose an expansion cohort to examine our novel 5-day regimen in patients receiving either neoadjuvant RT alone or neoadjuvant RT following neoadjuvant chemotherapy. The goal of this expansion cohort is to compare toxicity outcomes in patients receiving neoadjuvant chemotherapy with patients receiving radiotherapy alone. Should the rate of toxicity be similar in each cohort, then the 5-day approach can become incorporated as a standard-of-care for all patients regardless of the use of neoadjuvant chemotherapy.

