### **SAMPLE SIZE JUSTIFICATION:**

The original study was designed to test for a 20% absolute improvement in the rate of grade  $\geq 2$  radiation morbidity (subcutaneous tissue fibrosis, joint stiffness, or edema at 2 years ( $\pm 3$  months) from 37% in the preoperative RT arm of the CAN-NCIC-SR2 study to 17% which requires 41 patients per cohort with 5% type I error and 80% statistical power. Allowing for 20% of patients being ineligible or not analyzable at 2 years, the total sample size needed is 51 patients. **The study met this initial endpoint(6).**

**The expansion cohort** of this study aims to evaluate non-inferiority of major wound complication rate in cohort B (neoadjuvant chemotherapy and radiotherapy) versus patients in cohort A (radiotherapy alone). One-sided two-sample proportion test will be carried out to assess the non-inferiority of major wound complication rate in cohort B compared to cohort A. According to a recent study on rates of wound complications in patients receiving preoperative RT(8), we assume the wound complication rate in cohort A to be 21% (79% success rate). We also assume that for every patient enrolled in cohort B, at least three patients will be enrolled in cohort A. With significance level 0.1 and power 80%, the enrollment of at least 41 patients in cohort B will enable us to detect a 15% increase in the wound complication rate of cohort B, which would translate to a 36%

wound complication rate (64% success rate)(9). A wound complication rate of 36% has previously been considered acceptable for patients receiving standard preoperative radiotherapy and surgery(2). We set the minimum enrollment number to 123 for cohort A and 41 for cohort B. To account for a 20% rate of potential screening failures or participant dropouts, the total enrollment goal for the expansion cohort is 205 patients.

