#### **Primary Endpoint:**

Non-inferiority of major wound complication rate  
(cohort B vs cohort A)

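### The primary claim is non-inferiority, but the stated test has no margin and the sample size comes from a test of equal rates

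*Protocol*

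**What the plan says.** The claim is stated consistently. The Schema gives the primary endpoint as "Non-inferiority of major wound complication rate", B versus A, and the Sample Size Justification says that the expansion cohort "aims to evaluate non-inferiority of major wound complication rate in cohort B" relative to cohort A.

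The analysis is stated twice. In the synopsis, Statistical Methods 1.1 says that the rates "in cohorts A and B will be assessed using one- sided two-sample proportion test". The Sample Size Justification adds the purpose: "One-sided two-sample proportion test will be carried out to assess the non-inferiority". Neither place gives a margin, a null hypothesis or a decision rule, and Section 10 does not describe the primary test.

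On size, the Sample Size Justification states "we assume the wound complication rate in cohort A to be 21% (79% success rate") and at least three cohort A patients for each cohort B patient. Of the cohort B minimum of 41, at a 0.1 level and 80% power, it says that this "will enable us to detect a 15% increase in the wound complication rate of cohort B", that is, to 36%. Reference 9, cited there, is R's power.prop.test. The next sentence says that 36% has been regarded as acceptable with standard preoperative radiotherapy and surgery.

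The Protocol Synopsis states the consequence: "Should the rate of toxicity be similar in each cohort, then the 5-day approach can become incorporated as a standard-of-care for all patients".

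**The concern.** In a non-inferiority test with a 15-point margin, a 15-point excess in B is the null hypothesis, and rejecting it supports the claim. In a test powered to detect a 15-point increase, equal rates are the null and the 15-point excess is the alternative. Rejecting that null shows harm; failing to reject it shows nothing in particular. The protocol attaches a non-inferiority claim to a power statement for detecting a difference.

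The two tests can give opposite answers from the same data, and the protocol does not say which governs. Their error rates also sit in different places. The 0.1 significance level limits a false claim of non-inferiority only if the null is shifted by the margin. If the null is equal rates, 0.1 limits a false finding of harm, and a false claim of non-inferiority is governed by the power. This comparison decides whether the 5-day approach is put forward regardless of neoadjuvant chemotherapy.

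**Working it through.** **Inputs (Sample Size Justification).** pA = 0.21; pB = 0.36; difference 0.15; alpha 0.1, one-sided; power 80%; A:B = 3:1; minimum 41 in B and 123 in A. Normal quantiles: z(0.90) = 1.2816, z(0.80) = 0.8416.

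**1. Where 41 and 123 come from.** For a one-sided test of equal rates with equal groups, the mean rate is 0.285:

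n per group = [1.2816·√(2·0.285·0.715) + 0.8416·√(0.36·0.64 + 0.21·0.79)]² / 0.15² = (0.8181 + 0.5298)² / 0.0225 = 80.76.

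The total is 161.5. A quarter is 40.4, rounded up to 41, and 3 × 41 = 123. The figure therefore matches an equality test with equal groups whose total was then split 1:3. The enrolment goal also reproduces: 164 / 0.8 = 205.

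The same equality test at a true 3:1 ratio (mean rate 0.2475) gives (0.6386 + 0.4499)² / 0.0225 = 52.7, so 53 in B. At 41/123 its power is 72.6%.

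**2. What a non-inferiority calculation gives.** Assume a 15-point margin and true rates of 21% in both cohorts; the protocol states neither. With unpooled variance at 3:1:

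n in B = (1.2816 + 0.8416)² · 0.21·0.79 · (1 + 1/3) / 0.15² = 44.3, so 45.

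A Farrington-Manning score calculation gives 50.3, so 51 in B and 153 in A. Neither gives 41.

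**3. Power of a margin-based test at 41/123, same assumptions.** Unpooled: SE = √[0.1659·(1/41 + 1/123)] = 0.0735, and power = Φ(0.15/0.0735 − 1.2816) = Φ(0.761) = 77.7%. Exact binomial enumeration gives 76.5% for the unpooled test and 74.3% for Farrington-Manning.

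**4. How often non-inferiority would be claimed at 41/123, with A at 21%.** The middle column applies only if a non-significant result of the plain test were taken as non-inferiority. All figures are by exact enumeration.

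| True rate in B | Plain test not significant | Farrington-Manning, margin 0.15 | Unpooled, margin 0.15 |
|---|---|---|---|
| 36% | 27.2% | 10.2% | 11.3% |
| 30% | 54.0% | 29.3% | 31.5% |

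Normal-approximation check of the 27.2%: 1 − Φ[(0.15 − 1.2816·0.0778)/0.0835] = 27.4%.

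**5. One data set, two answers.** Take 12/41 in B and 26/123 in A: 29.3% versus 21.1%, a difference of 8.1 points. The pooled z is 0.0813/0.0761 = 1.07, below 1.28, so no significant increase is found. The upper one-sided 90% limit is 0.0813 + 1.2816·0.0800 = 0.184. That is above 0.15, so non-inferiority is not shown.

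**The case against.** The best defence is that the Sample Size Justification expressly links the test to non-inferiority, and a one-sided test of two proportions can carry a null shifted by a margin. The text also gives 21%, 15 points and 36%, then calls 36% acceptable. That reads like the justification of a largest tolerable rate, so the margin can be recovered in substance. The choice of test statistic and interval method can properly be left to a statistical analysis plan.

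Much of this stands. A reader might infer that the protocol tells the analyst to conclude non-inferiority from a non-significant result. It does not say so, and the 27% is conditional on that reading. A reader might also take the one-sided test as aimed at a lower rate in B. Nothing in the text supports that, and it conflicts with the stated non-inferiority aim. Nor should 20% be taken off 41/123 to make the error rate look worse, because the goal of 205 is set so that 164 remain.

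What the defence does not answer is the power statement. Detecting an increase is the language of a test of equal rates, the cited function computes that test, and 41/123 reproduces from it. A later analysis plan with a margin would supply the missing hypothesis, but it would contradict the size and power that the protocol already fixes.

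**Conclusion.** The stated analysis and sample size do not match the stated claim. The fault is more than missing detail: the margin and the shifted null are absent, and the power statement describes a different test. A 15-point margin is a reasonable inference from the text, but no more than that.

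If non-significance of the plain test were taken as non-inferiority, the claim would be made 27% of the time at 41/123 when B is truly 36% and A 21%, against about 10% (10.2% to 11.3%, by method) for a margin-based test at one-sided 0.10. Under a margin-based test, the 80% power figure does not hold at 41/123: it is about 74% with Farrington-Manning and 76% to 78% with unpooled variance. These power figures assume a 15-point margin and a true rate of 21% in both cohorts. Because this is the trial's primary comparison, it should be corrected before the analysis.

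**What to change.** In Statistical Methods 1.1 and the Sample Size Justification:

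- State H0: pB − pA ≥ 0.15 against H1: pB − pA < 0.15 at one-sided alpha 0.10, if 15 points is the intended margin, and justify that margin.
- Conclude non-inferiority only if the upper one-sided 90% confidence limit for pB − pA is below 0.15. The interval method is for the sponsor to choose. Add that a non-significant difference is not evidence of non-inferiority.
- Replace the wording about detecting a 15-point increase, and the equality-test basis for the size.
- Restate the power at 41/123 for the chosen test in place of 80%, with the assumed true rates.

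The cost is rewording in two places and a less favourable stated power. No added enrolment is required if the power is restated. Keeping 80% would instead raise the minimum in B to 45 (unpooled) or 51 (Farrington-Manning), with three times as many in A.

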### **2. Analysis of secondary endpoints**

2.1 Interim Reports for the Primary Endpoint grade  $\geq 2$  radiation morbidity (subcutaneous tissue fibrosis, joint stiffness, or edema) at 2 years. Interim reports will be prepared yearly until the results of the study are published. In general, the interim reports will contain information about patient accrual rate with projected completion dates, status of QA review and compliance rate of treatment per protocol, and the frequencies and severity of toxicity.

2.2 Analysis of efficacy with 5 secondary endpoints (local control, regional control, distant control, progression-free survival, and overall survival)

2.2.1 Kaplan-Meier analysis will be carried out and used to estimate the local control, regional control, distant control, progression-free survival, and overall survival rates.

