### **3. Analysis of exploratory endpoints**

3.1 The association between these 5 secondary endpoints and potential predictors (tumor size at diagnosis, tumor grade, tumor depth, tumor immune infiltration, patient age, patient sex) will be assessed by Cox proportional hazards model.

3.2 The association between germline mutations and response, toxicity and cancer outcome will be investigated using logistic regression model.

3.3 The impact of radiation on local and systemic immune responses will be evaluated using tumor and blood specimens, and these immunologic changes will be related back to patient outcomes.

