### **1.2 Secondary objectives**

#### **1.2.1 Secondary endpoints:**

Grade  $\geq 2$  radiation morbidity (subcutaneous tissue fibrosis, joint stiffness, or edema) at 2 years

Evaluate local control, regional control, distant metastasis, progression free survival, and overall survival

Evaluate the functional outcomes as assessed using the musculoskeletal tumor rating scale (MSTS) and the Toronto Extremity Salvage Score (TESS)

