### **3.0 PATIENT SELECTION**

#### **3.1 Conditions for patient eligibility**

- 3.1.1 Histologically confirmed soft tissue sarcoma of the extremity/trunk
- 3.1.2 Planning to undergo standard preoperative radiotherapy
- 3.1.3 Resectable primary lesion (patients with pre-existing metastasis will be included if their primary is still going to be resected)
- 3.1.4 Age  $\geq 12$
- 3.1.5 KPS  $\geq 70$  or ECOG of 0 - 2
- 3.1.6 If a woman is of childbearing potential, a negative serum or urine pregnancy test must be documented.

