## 10.0 STATISTICAL CONSIDERATIONS

### 10.1 Statistical considerations

1. Interim Reports for the Secondary Endpoint Grade  $\geq 2$  radiation morbidity (subcutaneous tissue fibrosis, joint stiffness, or edema) at 2 years

Interim reports will be prepared yearly until the results of the study are published. In general, the interim reports will contain information about patient accrual rate with projected completion dates, status of QA review and compliance rate of treatment per protocol, and the frequencies and severity of toxicity.

2. Estimation of Secondary Endpoints Related to the safety and efficacy

Cumulative incidence approach (K-M plots and COX proportional hazard modeling) will be used to estimate the local failure, regional failure, distant metastasis, progression-free survival, and overall survival rates.

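### Kaplan-Meier is named for local, regional and distant control, while section 10.1 labels the same method cumulative incidence; if deaths without failure are censored, failure risk is overstated

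*Protocol*

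**What the plan says.** Two places in the protocol name the estimator for the five secondary efficacy endpoints.

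- Synopsis, Statistical Methods, item 2.2.1: "Kaplan-Meier analysis will be carried out and used to estimate the local control, regional control, distant control, progression-free survival, and overall survival rates". All five endpoints are treated alike.
- Section 10.1, item 2: "Cumulative incidence approach (K-M plots and COX proportional hazard modeling) will be used to estimate the local failure, regional failure, distant metastasis", and the sentence goes on to progression-free and overall survival.

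Section 1.2.1 lists the endpoints only: "Evaluate local control, regional control, distant metastasis, progression free survival, and overall survival". Neither methods paragraph mentions death as a competing event or says whether death is censored or counted.

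Both eligibility lists admit patients who already have metastases. Section 3.1.3 reads "patients with pre-existing metastasis will be included if their primary is still going to be resected", and the synopsis has the same rule. The distant endpoint is listed without any restriction on who enters it.

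**The concern.** Progression-free and overall survival count death as an event in their usual sense, so Kaplan-Meier suits them. Local, regional and distant failure usually do not. A patient who dies free of local failure can no longer have one, but Kaplan-Meier with that death censored treats the patient as if failure could still occur later. One minus Kaplan-Meier then describes failure in a setting where nobody dies, and is too high as a statement of how many patients actually fail.

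Section 10.1 adds an internal disagreement. Its label promises cumulative incidence, but neither tool in the brackets delivers it when deaths compete. Kaplan-Meier is a different estimator, and a Cox model with deaths censored gives cause-specific hazards, not failure probabilities. An analyst who follows item 2.2.1 and one who follows the label in 10.1 would report different numbers.

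What is at stake is the accuracy of the reported failure rates for a shortened regimen. With the failure hazard held fixed, the error grows with mortality. It would be expected to be larger in cohort B, since the synopsis ties neoadjuvant chemotherapy to the highest-risk disease, and in patients with metastases at entry. The latter also cannot have a first distant failure after entry, so their place in the distant endpoint needs to be settled.

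**Working it through.** The protocol states no failure rate, death rate or power for these endpoints, so there is no figure of its own to reproduce. The check is an illustration over assumed rates.

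**Inputs**

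- Time point: 5 years, from the synopsis: "follow-up will be performed every 6 months after the time of surgery for the 5 years after treatment".
- F: the 5-year value of one minus Kaplan-Meier. Assumed at 10%, 20% and 40%.
- D: the 5-year probability of death without the failure, if the failure could not occur. Assumed at 10% to 40%.
- Cause-specific hazards constant and independent.

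**Formulas**

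- Failure hazard: hf = −ln(1 − F)/5. Death hazard: hd = −ln(1 − D)/5.
- One minus Kaplan-Meier, deaths censored: 1 − exp(−5·hf) = F.
- True cumulative incidence: hf/(hf + hd) × [1 − exp(−5(hf + hd))].

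**Worked case, F = 10% and D = 40%**

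- hf = 0.0211 and hd = 0.1022, so hf/(hf + hd) = 0.171.
- 1 − exp(−5(hf + hd)) = 1 − 0.9 × 0.6 = 0.46.
- Cumulative incidence = 0.171 × 0.46 = 0.079, against 0.10 from one minus Kaplan-Meier.

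**True 5-year cumulative incidence**

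| One minus Kaplan-Meier | D = 10% | D = 20% | D = 30% | D = 40% |
|---|---|---|---|---|
| 10% | 9.5% | 9.0% | 8.4% | 7.9% |
| 20% | 19.0% | 18.0% | 16.9% | 15.8% |
| 40% | 38.1% | 36.2% | 34.2% | 32.0% |

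The absolute excess runs from 0.5 points (10% against 9.5%) to 8 points (40% against 32%). In relative terms it is about 5% at D = 10%, 11% at D = 20%, 17–19% at D = 30% and 25–27% at D = 40%.

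**Simulation.** With 164 patients ("We set the minimum enrollment number to 123 for cohort A and 41 for cohort B"; 123 + 41 = 164), 1,000 runs and censoring uniform between 2 and 8 years, mean Kaplan-Meier and Aalen-Johansen failure estimates were:

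- F = 10%, D = 20%: 10.0% against 9.0%.
- F = 10%, D = 40%: 10.0% against 7.9%.
- F = 40%, D = 10%: 40.1% against 38.2%.

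**Higher mortality.** With a local failure hazard of 5% per year, one minus Kaplan-Meier at 5 years is 1 − exp(−0.25) = 22.1%. The cumulative incidence is:

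- death hazard 15% per year: (0.05/0.20) × (1 − exp(−1.0)) = 15.8%;
- death hazard 25% per year: (0.05/0.30) × (1 − exp(−1.5)) = 12.9%.

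Those death hazards imply 5-year mortality of 1 − exp(−0.75) = 53% and 1 − exp(−1.25) = 71%.

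**The case against.** The case on the other side has several parts.

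*The bias is conditional.* It arises only if deaths without failure are censored and the curve is read as an actual failure probability. The protocol says neither, and event definitions may sit in a statistical analysis plan that is not at hand. A reader might infer that the reported rates are certain to be wrong; the text does not support that. What stands is that the protocol itself names the estimator twice, and in section 10.1 label and tool do not match. That is a stated choice, not an omitted detail.

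*The size may be small.* A reader might take 22.1% against 12.9% as the expected gap. That needs mortality of about 71% at 5 years, which the documents do not support: patients have a resectable primary and adequate performance status, and the design assumes at least three cohort A patients for each cohort B patient. With a Kaplan-Meier failure estimate of 10% and D of 10% to 20%, the gap is 0.5 to 1 point. This part of the objection stands in full.

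*No planned comparison is distorted.* A reader might infer that the comparison of cohorts A and B is biased. The only comparison planned between them is of major wound complications, and no benchmark for local control is fixed. Overstating failure also understates control, which is the cautious direction for a shortened regimen. This stands, and it limits the consequence to descriptive secondary results.

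*Distant control is not thereby undefined.* A reader might infer that it cannot be defined for patients with metastases at entry. An analysis plan could leave them out of the risk set or count new distant progression. What stands is that the protocol admits them and does not exclude them from this endpoint.

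*The Cox models are not at fault.* The exploratory item beginning "The association between these 5 secondary endpoints and potential predictors" concerns associations, for which cause-specific hazards are a legitimate target.

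**Conclusion.** The point holds in a limited form. Item 2.2.1 and section 10.1 need to be reconciled, because 10.1 promises cumulative incidence and specifies an estimator that does not give it when deaths compete. If deaths without failure are censored, the direction of the error is certain: one minus Kaplan-Meier is never below the cumulative incidence, and exceeds it once such deaths precede later failures. The size rests wholly on assumed failure and death rates with constant, independent hazards. It is about 0.5 to 2 points for a Kaplan-Meier failure estimate of 10%, and 2 to 8 points for 40%, across 10% to 40% competing mortality. Larger mortality in cohort B is an expectation drawn from its description as higher risk, not a figure in the protocol. The number of patients with metastases at entry is also not given. The change is worth making because it is nearly free.

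**What to change.** Give item 2.2.1 and section 10.1 the same text:

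- Estimate local, regional and distant failure by Aalen-Johansen cumulative incidence, with death without that failure as the competing event.
- Keep Kaplan-Meier for progression-free and overall survival.
- Restrict the distant-metastasis endpoint to patients without metastasis at registration.

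The cost is wording and standard software. No extra data collection is required for the estimator, and the study calendar already schedules a pre-study chest CT, which identifies chest disease at entry. The one downside is that slightly fewer patients enter the distant-metastasis analysis.
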